### Cluster randomised controlled (main) trial

#### Eligibility criteria

The current intervention has been developed for universal samples [42], in that it aims to provide population-wide benefits, irrespective of an individual’s level of risk or other relevant factors (e.g., type of sport, competition level). Therefore, increased risk for body image concerns or sports dropout are not inclusion criteria for this trial. Eligible participants will be girls aged 11–17 years old who play sport, English speaking, and US residents. Eligibility criteria will allow for different sport types (e.g., individual, team, aesthetic, non-aesthetic) and competition level (e.g., recreational, competitive). Coaches will be eligible to deliver the intervention, provided they currently occupy a coaching role (e.g., a coach at a school or sport recreational centre) and have a stable and ongoing relationship with the girls who will receive the intervention. Coaches and/or the organisations delivering the intervention will need to be available during both “Block A” (intervention condition) and “Block B” (waitlist control), with condition allocation masked from participants.

#### Measures

Research measures are presented in Table 4. One measure was purpose-built for the current research (i.e., girls’ comprehension of the intervention content). The remaining measures have been validated and widely used among adolescent girls, particularly in the US.

**Table 4 Tab4:** Research outcomes and internal consistencies

Demographics	Age, gender identity, ethnicity, race, disability, state and region of residence, years playing sport	T1
Primary outcome		
Body Esteem	Body Esteem Scale for Adolescents & Adults (BESAA) [38] Appearance Esteem (AE; 10 items; e.g., I like how I look in photos) and Weight Esteem (WE; 8 items; e.g., I am satisfied with my weight) subscales Mean subscale scores range between 0 (never) and 4 (always). Higher scores reflect higher esteem The BESAA has shown good internal consistency reliability (Cronbach’s α = 0.76–0.96) and evidence of validity (correlations with self-esteem) in prior research conducted with adolescents [38, 43] The BESAA has been shown to detect change in body esteem at post-intervention [40, 44] and 1–6-month follow-up [40, 41, 45, 46] in interventions targeting adolescent girls	T1–T4
Secondary outcomes		
Body Appreciation	Body Appreciation Scale – 2 (BAS–2) [37] 10 items related to body appreciation (e.g., I take a positive attitude towards my body) Mean subscale scores range between 1 (never) and 5 (always). Higher scores reflect higher body appreciation The BAS–2 has shown good internal consistency reliability (Cronbach’s α = 0.86–0.93) and evidence of validity (correlations with self-esteem, body pride, life satisfaction) in prior research conducted with adolescents [46, 47] The BAS–2 has been shown to detect change in body appreciation at post-intervention [48] in interventions targeting adolescent girls	T1–T4
Resisting Objectification	Experience of Embodiment Scale (EES) – Resisting Objectification Subscale (RO) [49] 4 items related to inhabiting the body as a subjective site vs. as an objectified site (e.g., I focus more on what my body can do than on its appearance) Mean subscale scores range between 1 (strongly disagree) and 5 (strongly agree). Higher scores reflect greater resistance to objectification The RO subscale has shown good internal consistency reliability (Cronbach’s α = 0.71) and evidence of validity (correlations with body esteem, self-esteem) in previous research [49] The EES has been shown to detect change in embodiment at post-intervention and 3–12-month follow-up [17] in interventions targeting adolescent girls	T1–T4
Attuned Self-Care	Experience of Embodiment Scale (EES) – Attuned Self-Care Subscale (ASC) [49] 7 items related to the degree of attunement and responsiveness to the embodied self and its physical, emotional, relational, aspirational, and spiritual needs (e.g., I make sure I listen to my body and its needs [e.g., rest when I am tired, eat when hungry, leave when I feel unsafe, relax when stressed]) Mean subscale scores range between 1 (strongly disagree) and 5 (strongly agree). Higher scores reflect greater attunement to self-care The ASC subscale has shown good internal consistency reliability (Cronbach’s α = 0.75) and evidence of validity (correlations with body esteem, self-esteem) in previous research [49] The EES has been shown to detect change in embodiment at post-intervention and 3–12-month follow-up [17] in interventions targeting adolescent girls	T1–T4
Sports Enjoyment	Sources of Enjoyment in Youth Sport (SEYS) [39] 28 items related to six domains that elicit enjoyment among athletes (i.e., self-referenced competency [e.g., Playing well compared to how I’ve played in the past]; other-referenced competency and recognition [Doing skills other kids my age cannot do]; effort expenditure [Working hard in practice]; competitive excitement [Hearing the crowd cheer during a close game, match or race]; affiliation with peers [Being with friends on my team]; positive parental involvement [Getting encouragement from my parents]) Mean subscale scores range between 1 (strongly disagree) and 5 (strongly agree). Higher scores reflect greater enjoyment with this domain The SEYS has shown good internal consistency reliability (Cronbach’s α = 0.65–0.85) in previous research [39] The SEYS has been shown to detect change in enjoyment levels within domains at post-intervention in interventions targeting women [50] and differences in enjoyment among children and adolescents participating in individual and team sports [51]	T1–T4
Positive and Negative Affect	Positive and Negative Affect Scale (PANAS) [52] 10 items related to emotive states (5 positive [e.g., joyful]; 5 negative [e.g., scared]) Positive and negative affect subscale scores range between 1 (not at all) and 5 (extremely). Higher scores reflect greater positive or negative affect The PANAS has shown good internal consistency reliability (Cronbach’s α = 0.82–0.86) in previous research [52] The PANAS has been shown to detect change in affect at post-intervention [40, 53] in interventions targeting children and adolescents	T1–T4

T1 = Baseline; T2 = Post-Intervention; T3 = One-Month Follow-Up; T4 = Three-Month Follow-Up

#### Participant recruitment and procedure

A community sample of a minimum of 1,036 girls aged 11–17 years from diverse ethnic, geographic, and socio-economic backgrounds will be recruited for the main trial via a US recruitment partner who specialises in health education in school and community settings. Recruitment will occur in the 6 months prior to the trial start date (i.e., September 2022–February 2023) and will involve the following steps: 1) circulation of an online survey containing study information and an expression of interest and screening questionnaire (e.g., *Do you coach girls between 11–17 years old?*; *What is the estimated number of girls between 11–17 years that you will be coaching between February–July 2023?*) via the recruitment partner’s social media platforms and emailing lists; 2) following screening, eligible coaches and/or organisations will be invited to an information session held by the recruitment partner, where attendees will received a more detailed overview of the intervention and research tasks; and 3) provided coaches and/or organisations feel comfortable with, and confident that they can achieve, the research tasks, they will schedule an onboarding call with the third author (AT).

Following the onboarding process, organisations will be randomised into either the intervention (Block A) or waitlist control (Block B) condition (see Fig. 1 for participant flow). Those assigned to Block A will be advised to schedule the intervention between the 6^th^ February and 2^nd^ April 2023, while those assigned to Block B will be advised to schedule their delivery after the 2^nd^ July 2023. Three weeks prior to intervention delivery, coaches and parents will complete informed consent via an online survey. Following parental consent, girls in both conditions will complete informed assent and baseline assessments of primary and secondary outcomes via an online survey one week prior to intervention delivery. Girls will be encouraged to complete the surveys in the privacy of their homes; however, coaches agreed to make surveys accessible immediately before session one (e.g., girls will attend 20 min early and complete via a mobile device), should girls have difficulty completing the survey on their own accord. The intervention will be delivered in the team’s usual practice space, with logistics regarding equipment and space accessibility coordinated and confirmed with coaches during the onboarding call with the research team. At the end of the intervention period (i.e., 3 weeks), both conditions will be assessed on primary and secondary outcomes, and again at 1-month and 3-month follow-up. Following the final assessment, the waitlist control group will complete the intervention; however, their engagement will not be monitored or assessed. Lastly, to compensate participants for their time, they will receive an electronic voucher, with girls receiving US$60, coaches receiving $100, and organisations receiving $200.

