***Secondary outcome measures***						
*Body Appreciation*		X		X	X	X
*Attuned Self-Care*		X		X	X	X
*Resisting Objectification*		X		X	X	X
*Sports Enjoyment*		X		X	X	X
*Positive and Negative Affect*		X		X	X	X
*Intervention Fidelity (Coaches’ Delivery and Athletes’ Comprehension)*				X		
*Intervention Attendance*				X		

Findings from the co-creation (see section Cluster randomised controlled (Pilot) trial) and initial pilot (see section Co-creating the intervention) informed the final protocol for the cluster randomised controlled trial (Fig. 1), which will compare BCA to a waitlist control condition (i.e., participate in sport as usual). This is a pragmatic trial conducted in settings similar to the “real world” (i.e., adopts a sport setting, coach-led delivery, delivered during typical sport practice, no strict inclusion or exclusion criteria for athletes, comparison to usual sports participation) [28]. Participants in the intervention condition will complete three 60-minute sessions over three consecutive weeks. At completion of the final follow-up survey, girls and coaches in the control condition will participate in the intervention; however, their participation will not be monitored or evaluated.

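### The only baseline fallback described is tied to session one, which the control arm does not hold until after its final assessment, so setting and completeness of the baseline covariate may differ by arm

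*Protocol article*

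**What the plan says.** All of this comes from the Protocol article.

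- **Default setting.** Participant recruitment and procedure makes home the preferred place for all girls: "Girls will be encouraged to complete the surveys in the privacy of their homes".
- **Timing.** The same section says that "girls in both conditions will complete informed assent and baseline assessments of primary and secondary outcomes via an online survey one week prior to intervention".
- **Fallback.** It then adds that "coaches agreed to make surveys accessible immediately before session one (e.g., girls will attend 20 min early and complete via a mobile device", to be used "should girls have difficulty completing the survey on their own accord". No other fallback is described.
- **When session one happens.** "Those assigned to Block A will be advised to schedule the intervention between the 6^th^ February and 2^nd^ April 2023", whereas "those assigned to Block B will be advised to schedule their delivery after the 2^nd^ July 2023". The text after Table 2, in The present paper, agrees: "At completion of the final follow-up survey, girls and coaches in the control condition will participate in the intervention".
- **Order of events.** Organisations are randomised after onboarding, before consent and baseline. Table 2 likewise puts randomisation at enrolment and the baseline visit under the post-allocation heading.
- **Use of baseline.** Data analyses enters the baseline level of each outcome as a covariate in the mixed models and in the ANCOVAs at T2, T3 and T4.

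**The concern.** The fallback hangs on an event that only one arm has before its last assessment. A coach who follows the text in Block A has an occasion to offer; a coach who follows it in Block B does not. Because this happens after allocation, randomisation does not balance it.

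Two things could then differ by arm. The first is setting: some Block A girls would give self-reports on body image at the practice venue shortly before a session on that subject, while Block B girls would answer at home. The second is completeness: girls who are hard to reach could be recovered in Block A with no described route in Block B. The baseline score adjusts the primary T2 comparison, so an arm-specific shift in it carries into the estimated effect. Analyst masking does not remove such a shift, and oversampling cannot correct a bias.

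**Working it through.** **1. The plan's own figure, to confirm the inputs.** Statistical power gives d = 0.2, ICC 0.02, 15 athletes per group, baseline-outcome correlation 0.6, alpha 0.05 and 90% power. Two-sided alpha is assumed here.

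- Unadjusted n per arm: 2 × ((1.960 + 1.282)/0.2)² = 525.4
- ANCOVA factor: 1 − 0.6² = 0.64
- Design effect: 1 + 14 × 0.02 = 1.28
- 525.4 × 0.64 × 1.28 = 430.4, so 431 per arm and 862 in total

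The stated 864 is reproduced closely; 432 per arm gives 90.1% power. So 0.6 and 0.2 are fair inputs for what follows.

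**2. Is the fallback open to both arms?** Block A sessions run from 6 February to 2 April 2023. Block B is told to deliver after 2 July 2023, following its final assessment. At T1, therefore, a session one lies ahead within the assessment period only in Block A.

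**3. Effect of a setting shift.** The adjusted difference is (mean outcome A − mean outcome B) − b × (mean baseline A − mean baseline B). If a fraction f of Block A uses the slot and answers there shift by m SD, Block A's mean baseline moves by f × m. The adjusted difference moves by −b × f × m.

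- b = 0.6: the plan's correlation, used as the standardised slope.
- f up to 0.27: an assumption. In Pilot findings 19 of 26 girls completed baseline, so 7/26 = 27% did not. The calculation supposes that every such girl would use the slot.
- m = 0.1 to 0.3 SD: an assumption with no source in the article.

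Results:
- 0.6 × 0.27 × 0.1 = 0.016 SD, and 0.016/0.2 = 8% of the planned effect
- 0.6 × 0.27 × 0.3 = 0.049 SD, and 0.049/0.2 = 24% of the planned effect

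More favourable answers at the venue would raise Block A's baseline and understate the effect. Less favourable answers would overstate it.

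**4. Effect of unequal completeness, as a side check.** Assume 80% of 518 (414) are usable in Block A, with the same ICC and correlation.

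| Block B shortfall (percentage points) | Power |
|---|---|
| 0 | 88.9% |
| 5 | 87.9% |
| 10 | 86.7% |
| 20 | 83.8% |

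Precision suffers only modestly. Selection is the other route: if 5-20% of analysed Block A girls were kept only through the fallback and differed by 0.1-0.3 SD in adjusted outcome, the bias would be 0.05 × 0.1 = 0.005 to 0.20 × 0.3 = 0.06 SD. These inputs too are assumptions.

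**The case against.** The strongest reply is that session one is loose shorthand. The sentence on timing sets baseline in both conditions one week ahead of delivery. Read literally for Block B, that falls around or after 2 July, which cannot be meant. Table 2 gives one schedule in days from baseline for everyone. The fallback may have been intended for a common calendar point too. This stands as a possible reading, but it does not settle the matter: the article names no such point for Block B, and a coach working from the text would have nothing to offer there.

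Other parts of the reply also stand:

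- **A reader might infer that baseline is in fact collected differently and more completely in Block A.** The article does not show this. Home is the default in both arms, the fallback is conditional, and no completion rates by arm are given for the main trial. Pilot completion was nearly equal (10/13 and 9/13), and onboarding has since been lengthened from 3 to 6 months to reduce baseline attrition.
- **A reader might infer that Block B girls are denied any help, or that no venue access exists at T2-T4.** The article is merely silent on both, and a condensed article may leave such detail to the full protocol.
- **A reader might infer that coaches see the answers.** The text says only that access is provided, with early arrival and a mobile device as an example. Hypotheses are also masked from participants.
- **A reader might assume heavier use of the slot.** No uptake was observed in the pilot, and its non-completion (3/13 = 23% in the intervention arm, 27% overall) gives no support for more than about 27%.

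**Conclusion.** The point holds as a risk created by a stated procedure. The one fallback on the page depends on an event that only the intervention arm has at baseline, it operates after randomisation, and it touches the covariate of every planned model. This is more than omitted detail, because the article chose the anchor and the anchor does not work for Block B.

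The affected group is the unknown subset of girls who do not complete at home. With up to about 27% using the slot, a shift of 0.1-0.3 SD and a slope of 0.6, the adjusted T2 difference would move by up to about 0.016-0.049 SD (8-24% of d = 0.2), in either direction. Both uptake and shift are assumptions; lower uptake reduces the figure in proportion. The documents do not support a claim that baseline will differ between arms, only that the procedure as written allows it.

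**What to change.** Replace the wording that ties the fallback to session one with a slot offered in both blocks at the same point relative to baseline. One workable form is 20 minutes before a usual practice in the baseline week, completed privately on a mobile device. Record for each survey whether it was completed at home or at the venue, so that setting and completion can be reported by arm. If any venue fallback is used at T2, T3 or T4, make it the same in both blocks.

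The cost is small: Block B coaches host a short slot at a practice they already hold, and the survey gains one field. No extra staff are needed, and no figure in the sample size changes.

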#### Randomisation and blinding

Randomisation will occur at the group level (1:1). The randomisation sequence will be generated using a computer software, with clusters randomised into the intervention or control condition. Randomisation will be conducted by an experienced researcher who is external to the authoring research team and the conditions will be masked. Throughout the recruitment and onboarding processes, group allocation will be masked to participants. The intervention group will be referred to as Block A and the control condition referred to as Block B. Coaches and/or organisations delivering the intervention will be advised that two scheduling blocks have been created due to the magnitude of participants. Study hypotheses will also be masked from participants. Lastly, data analysts will be unaware of condition allocation (dummy coded) when conducting statistical analyses on primary and secondary outcomes.

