With respect to the feasibility of conducting a two-armed, cluster randomised controlled trial in the US, the pilot highlighted several key limitations of the protocol, which required remedying before the main trial. First, the recruitment and onboarding period was lengthened from 3 to 6 months. This was based on feedback from coaches and their organisations that more time was needed to: 1) understand the research requirements; 2) get executive approval (if necessary) from the head of their organisation; 3) identify eligible participants; and 4) schedule the research tasks (i.e., surveys and intervention delivery). Further, due to the seasonal nature of some sports (i.e., soccer, lacrosse), this process became more complex for coaches, and therefore additional time was needed for troubleshooting. This modification aims to improve the onboarding of organisations, coaches, and girls, and subsequently reduce the attrition rates observed at baseline. Second, eligibility criteria were expanded to include school sports. Initially, only sport-based youth development organisations were targeted, as initial dissemination and implementation efforts were aimed at organisations that are typically underserved; however, due to the global COVID-19 pandemic, numerous organisations were experiencing funding and staffing cuts and therefore could not dedicate the time and resources to research participation. Therefore, the main trial is open to school athletic departments alongside youth development organisations, with the continued aim of targeting schools in underserved communities.

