#### Statistical power

A meta-analysis of 31 studies evaluating interventions that target the intersection of body image and movement experiences among girls and women via randomised controlled trials reported a mean effect size of Cohen’s *d* = 0.18 on body image, which can be interpreted as a small-to-medium effect size. Based on conservative *d* = 0.2, an ICC of 0.02 within intervention delivery groups (as informed by a similar cluster trial of a body image intervention Craddock, Budhraja, Garbett, Nasution, Gentili, Rizkiah, Saraswati, Medise, White, Diedrichs & Williamson: Randomised Control Trial of Dove Confident Me Indonesia: Single Session. Forthcoming]), and an approximate distribution of 15 athletes per delivery group, a total sample size of 864 athletes (*N* = 432 per arm) would provide 90% power over a correlation between baseline and outcome data at T2 or about 0.6, considering alpha = 0.05. We will oversample to mitigate the effects of loss at post-intervention due to athletes’ absence or any other logistical difficulty. Therefore, the ideal sample size will be increased by 20%, leading to a minimum target of approximately 1,036 athletes (518 per randomised arm).

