#### Data analyses

Data preparation, assessment of baseline equivalence, hypothesis testing, and exploration will be undertaken using SPSS 28.0 (IBM Corp, 2021) and R Studio (R Core Team, 2021). Data will be screened to ensure scoring fidelity and data accuracy. Once the data validity checks are complete, scales’ scores will be calculated, score distributions will be assessed, and the data will be checked for outliers and any inaccurate influential observations. Missing data will be assessed across all outcomes and time points. Data will be analysed on an intention-to-treat basis and secondly using data from participants with at least 70% of the attention checks successful completed.

The primary analyses will be linear mixed models with random intercepts for all outcome measures (body esteem, body appreciation, self-objectification, attuned self-care, sports enjoyment, and affect). The models will include two main effects: study phase (i.e., repeated measures fixed effect factor with three levels: T2, T3, and T4), randomised arm (i.e., between-subjects fixed effect factor with two levels: intervention and control), as well as baseline levels of the outcome as a covariate. The model will also see two two-way interactions (i.e., randomised arm by study phase, randomised arm by baseline). Analyses will be run on an intention-to-treat basis, both with and without clusters including a random effect (i.e., intervention delivery group), in order to identify their potential significant impact [54].

For each outcome measure, a priori ANCOVAs will compare the two randomised arms at T2, controlling for baseline measures as covariates. These analyses will be repeated at T3 and T4. If the homogeneity of regression lines assumption is violated, the ANCOVA model will include a baseline by randomised arm interaction. Exploratory moderation and mediation analyses will be run to check whether any differences in intervention efficacy might be dependent on relevant demographic or baseline variables. To ensure valid statistical inferences, we will check for any potential assumption violation in all the models.

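### No balancing factor is named for a mixed set of organisations, and the listed primary model adjusts only for baseline outcome: avoidable chance imbalance in organisation type and age, but not bias or a wrong sample size

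*Protocol article*

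**What the plan says.** **Allocation.** Participant recruitment and procedure makes the organisation the unit that is randomised. Randomisation and blinding gives the level (group), the ratio (1:1), an external randomiser, masking, and this description of the sequence: "The randomisation sequence will be generated using a computer software, with clusters randomised into the intervention or control condition". It mentions no blocking, stratification, matching or minimisation. It also does not say that allocation is simple or unrestricted.

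**How the units differ.** After the pilot, "the main trial is open to school athletic departments alongside youth development organisations" (Pilot findings). Eligibility criteria admits girls aged 11 to 17, any sport type, and recreational or competitive level. The screening questionnaire asks for the expected number of girls, so expected size is known before allocation.

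**Model.** Data analyses sets out the terms: "The models will include two main effects: study phase" and randomised arm, then the baseline outcome as covariate, then arm by phase and arm by baseline. The model is run with and without a delivery-group random effect. The ANCOVAs at T2, T3 and T4 adjust for the baseline measure. Demographic variables enter only exploratory moderation and mediation analyses.

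**Size.** Statistical power requires 864 girls (432 per arm), raised to a "minimum target of approximately 1,036 athletes (518 per randomised arm").

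**The concern.** Far fewer units are randomised than girls. At 15 girls per delivery group, 1,036 girls make about 69 groups (1,036 / 15 = 69.1). The number of organisations is at most about that, and lower if some run several groups.

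With so few units, chance can place noticeably more schools, or more organisations with older girls, in one arm. If change in body esteem over the three weeks to T2 differs by setting or age, that imbalance moves the estimate in the one trial that is run. A reader then cannot easily separate it from the intervention effect. Organisation type and expected size should be known before allocation, and age is recorded at T1, so the imbalance could be prevented at allocation or adjusted for in the analysis. The article names no such step at allocation, and the model as listed does not include it.

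**Working it through.** **1. Reproduce the stated sample size.** All inputs come from Statistical power: "Based on conservative *d* = 0.2", "an ICC of 0.02 within intervention delivery groups", 15 athletes per delivery group, correlation 0.6, 90% power, and "considering alpha = 0.05" (taken as two-sided).

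- Design effect: 1 + (15 − 1) × 0.02 = 1.28.
- Variance factor after baseline adjustment: 1 − 0.6² = 0.64.
- n per arm = 2 × (1.960 + 1.2816)² × 0.64 × 1.28 / 0.2² = 430.4, so 431. The article states 432.
- Power at 432 per arm: 90.1%.
- 864 × 1.2 = 1,036.8, which matches the target of about 1,036.

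The stated figures reproduce.

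**2. What unequal arms cost.** Hold the total at 864 analysed. Power = Φ(0.2 / √[0.64 × 1.28 × (1/n₁ + 1/n₀)] − 1.96).

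| Split of girls | Power |
|---|---|
| 50:50 | 90.1% |
| 55:45 | 89.8% |
| 60:40 | 88.9% |
| 65:35 | 87.2% |
| 70:30 | 84.5% |

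**3. How unequal the arms might be.** The article gives neither the number of organisations nor the spread of their sizes, so these are assumed cases, simulated with 20,000 draws and 1,036 girls.

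| Case | Coin flip per organisation | Equal numbers of organisations per arm |
|---|---|---|
| 58 equal-sized: median / 95th percentile difference in girls | 107 / 250 | 0 / 0 |
| 30, size CV 0.5: median / 95th percentile difference in girls | about 144 / 412 | about 64 / 184 |

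A difference of 250 is a split of about 62:38 (643 against 393), where power is about 88%. A difference of 412 is about 70:30, where power is about 85%. A difference of 184 is about 59:41, where power is about 89%. The large differences arise only if each organisation is allocated by an independent coin flip.

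**4. Imbalance in organisation type under the favourable reading.** Take k organisations, half of them schools (an assumption), with exactly k/2 organisations per arm. The number of schools in the intervention arm, X, is then hypergeometric with population k, k/2 schools and k/2 drawn. The difference in school share between arms is |2X − k/2| / (k/2).

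| k | More than 20 points apart when | Probability |
|---|---|---|
| 30 | X ≤ 5 or X ≥ 10 | 14.3% |
| 40 | X ≤ 7 or X ≥ 13 | 11.3% |
| 58 | X ≤ 11 or X ≥ 18 | 11.4% |
| 70 | X ≤ 13 or X ≥ 22 | 5.5% |

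Simulation agrees to within about a point. With coin-flip allocation the probability is about 15% for 58 organisations and 32% for 30. The share here counts organisations. It equals the share of girls only if organisations are of equal size.

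**5. What such an imbalance could do.** If schools and youth organisations differ by γ standard deviations in T2 body esteem after baseline adjustment, an imbalance of δ in school share of girls shifts the unadjusted arm difference by γ × δ. The article gives no γ. As an assumed range, γ = 0.1 to 0.2 with δ = 0.20 shifts the estimate by 0.02 to 0.04, which is 10 to 20% of the planned d = 0.2. If γ is zero, nothing is lost.

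**The case against.** The strongest reply is that this rests on silence in a condensed article. Blocks and strata are commonly left to the full protocol, and 1:1 may well mean equal numbers of organisations per arm. That stands. A reader might infer from the text that allocation is a plain coin flip and that the arms may differ by hundreds of girls. The article does not say so, and with equal numbers per arm most of the size imbalance disappears.

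A reader might also infer that 518 per arm is unsupported. It is not. The figure is a recruitment target 20% above the 432 required, the 432 reproduces, and moderate inequality costs one to three points of power.

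A third tempting inference is bias. Randomisation removes it in expectation whether or not type, size or age is in the model. The analysis also adjusts for the baseline outcome, can carry a delivery-group random effect, and includes an assessment of baseline equivalence. The design effect of 1.28 already allows for ordinary differences between delivery groups. All of this stands.

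Finally, nothing in the article shows that organisation type or age predicts T2 body esteem once baseline is known. This limits the size of the point but does not remove it. Baseline adjustment covers only the part of a type or age difference already visible at T1, not a different course afterwards. The model is also written out term by term, so the absence of these covariates is a stated choice and not merely a detail left elsewhere.

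**Conclusion.** The point holds as a small, avoidable loss of precision and a risk of chance imbalance. It does not show bias, and it does not show an error in the sample size.

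If half the organisations are schools and the arms hold equal numbers of organisations, school share differs by more than 20 points in about 11 to 14% of allocations with 30 to 58 organisations. With 70 it is about 6%. The number of organisations and the proportion of schools are assumptions, because the article gives neither. The effect on the estimate depends on how far type and age predict the outcome beyond baseline, which is also not given.

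Whether allocation was restricted cannot be settled from the article. The firm part is the primary model, which as listed leaves such an imbalance unadjusted.

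**What to change.** 1. In Data analyses, add age (recorded at T1, Table 4) and organisation type (school or youth development) as fixed effects in the primary mixed model and in the T2 ANCOVA. Fix this before the data are analysed by arm, so that covariates are not chosen after the baseline-equivalence check.
2. In Randomisation and blinding, state whether allocation is restricted and by what. Put every factor used into the same models.
3. If allocation is not already restricted and has not yet taken place, block it within organisation type. If numbers allow, also block above and below the median expected number of girls from screening. The Discussion gives 22 February 2023 as the last opportunity to enrol, so this step may come too late. Steps 1 and 2 do not depend on it.

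The cost is small. Expected size and age are already planned data, and organisation type should be known from onboarding. The models lose one or two degrees of freedom at cluster level. With few organisations some strata may be thin, in which case stratify by type alone.
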